### 2.2 Sample size calculation

The sample size for this study was determined through a priori power analysis performed using G*Power software (version 3.1.9.7) (Faul et al., 2007). Based on previous research, the study employed an Analysis of Variance (ANOVA) with repeated measures in the calculations. We expected an effect size of 0.40, an alpha error of 0.05 and a power level (1–β) of 0.20. The analysis indicated that at least 36 participants would be necessary to achieve an adequate cohort size for the study. Taking into account the participant dropouts rate 10%, the final sample size for this study was set at 40 individuals, with 20 participants allocated to each group. This sample size is considered adequate to generate reliable and valid outcomes for the research.

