### 2.4 Procedure

Before the experiment, the demographic data of all subjects will be first collected. We then explained the experimental process, test actions, and precautions to the participants. Adequate time will be provided for them to acclimate to the experimental process, ensuring a comprehensive understanding of the experimental requirements. Subsequently, fNIRS equipment and sEMG sensors will be affixed to each participant.

The experimental protocol consists of three distinct motor tasks: level walking, ascending stairs, and descending stairs. Participants will perform three tasks in a random order, with each task being repeated three times. There will be a 5 min interval between tests to allow participants to rest adequately and ensure that the fNIRS spectral signals of each test return to the baseline. Tests will be conducted on the KOA patients first, followed by the healthy controls. During the level walking, the patients will be instructed to walk at a normal, comfortable self-selected speed (SSS) for 30 s each time, with SSS defined as the average velocity from three timed baseline walks. The stair program evaluation will use standardized stairs under the same SSS conditions, maintaining consistent handrail non-use protocol across groups. The staircase consisted of 10 steps, with each step having a height of 12 cm, conforming to the standard specification for steps in China. To mitigate speed-related confounding effects, healthy controls will be pace-matched to the patient cohort’s average speed under the same conditions. A schematic overview of the experimental protocol is depicted in Figure 2. During the test, if the participant experiences any discomfort (e.g., dizziness, or falls), the testing will be immediately stopped and undergo medical evaluation of whether to continue.

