### 2.6 sEMG data acquisition and preprocessing

A multi-channel wireless sEMG system (Ultium EMG, Noraxon, United States) will be employed to measure the activity of lower limb muscles during movement. This can reflect muscle activation and functional status. sEMG sensors are placed on the skin surface of target muscles to record the electrical signals generated during muscle contractions. Including a total of seven target muscles of right lower limb as follows: rectus femoris (RF), vastus medialis (VM), vastus lateralis (VL), biceps femoris (BF), tibialis anterior (TA), medial head of gastrocnemius (GM), and lateral head of gastrocnemius (GL). The sEMG sensor is placed at the most prominent part of the muscle belly, ensuring that the sensor positions did not interfere with normal movement. In addition, the sensor is wrapped with a skin membrane to prevent the sensor from loosening or falling during movement.

In this study, Script will be written using Matlab2019b version software to complete the batch processing of surface EMG data. Firstly, the EMG data will be filtered to eliminate various noises in the signal. Then, the DC bias is removed by means of deaveraging, followed by full-wave rectification of the pre-processed signal. The Hilbert transform is used to extract the signal envelope. To reduce individual differences, the Maximum Voluntary Contraction (MVC) will be used to normalize the EMG signals of each muscle (Chowdhury et al., 2013). The indices selected for this study included root mean square (RMS) and median frequency (MF) of frequency-domain features derived from fast Fourier transform.

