### 2.8 Statistical analysis

The statistical analysis of this study covers clinical indicators, muscle and brain activation. Statistical analysis will be conducted on clinical indicators and muscle activation using SPSS 21.0 Software (IBM Corporation, New York, United States). Continuous variables with normal distribution will be presented as mean ± standard deviation, while non-normally distributed variables will be shown as median and quartiles. Categorical variables will be reported as frequency. The normality test will be performed using Shapiro-Wilk test. An independent *t*-test is applied when demographic data follow a normal distribution. Otherwise, the Mann–Whitney’s U test will be applied. The Chi-square test will be used to compare sex. Muscle activation in different groups (KOA and HC) and tasks (level walking, ascending stairs, and descending stairs) will be analyzed using mixed ANOVA or non-parametric tests (for non-normality). For brain activation analyses, a flexible factorial design (FFD) in SPM will be employed to construct a mixed-effects model including groups (inter-subject factors) and tasks (intra-subject factors) to evaluate group main effects, task main effects and their interactions. SPM will be thresholded with cluster-level false discovery rate (FDR) correction (*p* < 0.05). To explore the correlation between brain activation (HbO concentration and β value) and clinical indicators (VAS and WOMAC) in KOA patients, a multiple linear regression analysis will be performed to calculate the Pearson correlation coefficient and RMS value. Additionally, a non-linear regression prediction based on the random forest algorithm will be used to assess the importance of regression between various brain regions, muscle characteristics, and clinical indicators. All statistical tests will use a significance level of 0.05, with corrections for multiple comparisons made using the Bonferroni adjustment.

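### Outside the brain maps the plan fixes single-step Bonferroni; Holm's method in the same families gives the same family-wise protection, never rejects less and can reject more

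*Protocol article*

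**What the plan says.** Section 2.8 closes with the general rule "All statistical tests will use a significance level of 0.05, with corrections for multiple comparisons made using the Bonferroni adjustment". It does not say which tests form a family.

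Two other statements in 2.8 limit its reach:

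- The brain activation maps have their own rule: "SPM will be thresholded with cluster-level false discovery rate (FDR) correction".
- The muscle data "will be analyzed using mixed ANOVA or non-parametric tests (for non-normality"), with group and task as factors.

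The possible size of a family comes from elsewhere in the article. Section 2.6 gives seven muscles ("Including a total of seven target muscles of right lower limb as follows") and two measures per muscle ("The indices selected for this study included root mean square (RMS) and median frequency (MF"). Section 2.4 gives "three distinct motor tasks: level walking, ascending stairs, and descending stairs", hence three task pairs. Section 2.2 sets the sample size with f = 0.40 and alpha 0.05. It arrives at 36 participants, raised to 40 (20 per group) for 10% dropout.

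**The concern.** Bonferroni holds every p-value in a family of m to 0.05/m, however many of the other hypotheses have already been rejected. Holm relaxes the threshold as hypotheses are rejected and keeps the same guarantee. A plan that names Bonferroni therefore accepts a stricter test with no extra control of false positives.

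In a study of 36 to 40 people this can decide which muscles are reported as different. The sample size reproduces only with an unadjusted alpha of 0.05, so any correction across muscles is a power cost that was not budgeted. Holm recovers part of that cost without adding participants.

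**Working it through.** **1. The plan's own figure.** For the between-groups test in a repeated-measures ANOVA, λ = N·f²·m / (1 + (m − 1)ρ). Inputs are f = 0.40 (section 2.2), m = 3 tasks (section 2.4) and two groups. ρ = 0.5 is assumed, because the article gives no value.

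- N = 36: λ = 36 × 0.16 × 3 / 2 = 8.64, power 81.5%. This is the smallest even N that reaches 80%, and 36 / 0.9 = 40. The plan's 36 and 40 reproduce.
- The match needs power 0.80. Section 2.2 prints "We expected an effect size of 0.40, an alpha error of 0.05 and a power level (1–β) of 0.20"; a power of 0.20 would give N = 8. The printed value is read here as β.
- The required N depends on ρ: 30 at 0.3, 36 at 0.5, 42 at 0.7.

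**2. Cost of single-step Bonferroni at N = 40.** λ = 40 × 0.16 × 3 / 2 = 9.6. On the three-task mean this is d = √9.6 / √10 = 0.98 with 20 per group.

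| Level | Power per effect |
|---|---|
| 0.05 | 85.5% |
| 0.05/3 = 0.0167 | 72% |
| 0.05/7 = 0.0071 | 60% |
| 0.05/14 = 0.0036 | 50% |

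**3. Why Holm protects equally.** Order the p-values. Compare the smallest with 0.05/m, the next with 0.05/(m − 1), and so on, and stop at the first failure. For m = 7 the thresholds are 0.0071, 0.0083, 0.0100, 0.0125, 0.0167, 0.0250 and 0.0500. None is below 0.05/7, so whatever Bonferroni rejects Holm rejects. If m₀ nulls are true, the first false rejection must occur while all m₀ are still in the list, so at a threshold of at most 0.05/m₀. Its probability is at most m₀ × 0.05/m₀ = 0.05, whatever the dependence.

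**4. Size of the gain.** Simulated two-group t-tests, d = 0.98 for each affected outcome, outcome correlation 0.5 (assumed), 20 per group:

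| Family | Truly different | Bonferroni, per effect | Holm, per effect | Holm family-wise error |
|---|---|---|---|---|
| 7 | 1 | 60% | 60% | about 4% |
| 7 | 3 | 60% | 63% | about 4% |
| 7 | 4 | 60% | 64–65% | about 3% |
| 7 | 7 | 60% | 72% | no true nulls |
| 14 | 7 | 51% | 54% | about 3% |
| 14 | 14 | 51% | 64% | no true nulls |

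With 18 per group (36 completers) the seven-muscle figures are 54% against 66% when all differ and 53% against 57% when four differ. The chance of detecting at least one true effect is essentially the same under both methods (for example 94% when all seven differ).

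**5. The tempting extension to task pairs.** For one outcome with three tasks, any two pairwise nulls together imply the omnibus null. A valid omnibus test followed by pairwise tests at 0.05 therefore controls error for that outcome. With one task differing by 0.5 SD (assumed) at N = 40, pairwise power is about 83–84% against 74% for Bonferroni. The protection does not carry across outcomes. Under the global null (N = 36, task and muscle correlations 0.5, Hotelling omnibus):

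| Outcomes | Omnibus test, then pairs at 0.05 | Bonferroni or Holm over outcomes × 3 pairs |
|---|---|---|
| 1 | 5% | about 4.5% |
| 7 | 24% | 4% |
| 14 | 36% | 4% |

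Even for one outcome, an uncorrected univariate omnibus test gave 6.4–6.5% under the two non-spherical covariances tried.

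**The case against.** The strongest reply is that nothing in 2.8 is wrong. Bonferroni is valid, simple and conservative, and Holm could be offered to any plan that names it. That stands: this is an efficiency improvement.

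A reader might infer three stronger things, and the article supports none of them.

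- **That every test is Bonferroni-adjusted.** The brain maps, the study's central analysis, are assigned cluster-level FDR in the same section.
- **That Bonferroni is fixed across seven muscles or 14 outcomes.** No family is defined, and the closing sentence fits post hoc task comparisons equally well. The 7- and 14-test figures are conditional on a reading. Holm's dominance holds for any family of two or more tests.
- **That real effects are lost for nothing.** The gain is nil when one muscle differs, about 3 to 5 points when three or four of seven do, and about 12 points only when all do. Bonferroni also brings simple simultaneous confidence intervals. Holm has no simple counterpart, and Bonferroni intervals shown beside Holm decisions may disagree with some of them.

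Nor does the three-task argument justify dropping adjustment for task pairs. It holds within one outcome with a suitable omnibus test, and would weaken existing control if Bonferroni was meant to span muscles. It also does not extend to group differences within each task: when only one task truly differs, testing these after a significant interaction gave family-wise error of 7–9%, against about 3% for Bonferroni.

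**Conclusion.** The point holds as a modest efficiency improvement for tests outside the SPM maps. Holm gives the same family-wise control under the same conditions, never rejects less, and can reject more. On the seven-muscle reading, power per affected muscle goes from about 60% to about 72% (all seven differ), to about 64–65% (four differ), or stays put (one differs).

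These figures rest on f = 0.40 applying to each affected muscle, on task and muscle correlations of 0.5, and on 20 per group. The error-control argument needs none of these assumptions. Results obtained with Bonferroni as planned would remain valid.

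**What to change.** In the last sentence of section 2.8, replace the Bonferroni phrase by: *using the Holm step-down adjustment, within the same families to which Bonferroni would have been applied; the SPM maps keep cluster-level FDR.*

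Use Holm for the task pairs too. Pairwise task tests that follow an omnibus test are acceptable only under three conditions:

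- the omnibus task p-values are themselves Holm-adjusted across outcomes;
- the follow-up pairwise tests stay inside that adjustment, so an outcome with a pair still unrejected does not release its share of alpha to the others;
- the omnibus test is multivariate or sphericity-corrected.

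The cost is one phrase, settled before data are seen, and a sorting step on p-values that SPSS already prints. No participants are added. The one drawback is on intervals: if simultaneous intervals are wanted, Bonferroni intervals can be reported with a note that they may not match every Holm decision.

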## 3 Discussion

This study systematically explores the differences in sensory-motor cortex activation patterns in patients with KOA under different walking environments. Specifically, it compares neural activation characteristics during level and stair walking. Using fNIRS, the research will reveal changes in brain activation in KOA patients across different exercise environments, providing new insights into the pathological mechanisms of KOA. In addition, this study will provide potential targets for clinical intervention in KOA by investigating the connection between changes in patient brain activation and clinical indicators.

The feasibility of this study is underpinned by the robust methodology and the use of advanced neuroimaging techniques. The fNIRS system, with its ability to measure hemodynamic changes in the brain, offers a non-invasive and portable means of assessing cortical activation (Menant et al., 2020; Huo et al., 2023). Unlike fMRI, which imposes strict motion restrictions and requires a shielded laboratory environment, fNIRS enables non-invasive monitoring of cortical hemodynamic responses in naturalistic settings, including free movement and social interactions (Pereira et al., 2023). Cao et al. (2025) used FNIRS to study the brain activation characteristics of anterior cruciate ligament reconstruction (ACLR) patients during a repetitive upstairs task. The research results indicate that ACLR patients exhibit significant negative activation in the ipsilateral pre-motor cortex, supplementary motor cortex, and primary somatosensory cortex, while this feature was not observed in healthy individuals. The author believes that interventions targeting these brain regions may represent a novel rehabilitation approach. Another study used fNIRS to collect brain activation from KOA patients and healthy people while walking under exercise, and found that compared with comfortable walking, KOA patients had a significant increase in activation of the prefrontal cortex during disturbed walking, and this increase was more significant in healthy elderly women (Bishnoi et al., 2024). fNIRS portability and tolerance to motion artifacts make it ideal for investigating dynamic processes in real-world scenarios (Zinos et al., 2024). In addition, this study combined with sEMG measuring muscle activity could comprehensively evaluate the motor and functional status in KOA patients (Wang et al., 2023; Huang et al., 2025). This provides a physiological basis for near-infrared brain functional imaging, revealing the complex interaction mechanisms between peripheral muscles and the central nervous system in motor control, and analyzing nervous system adaptation processes at the muscle level. Huang et al. (2025) used fNIRS and sEMG technology to study the complex relationship between brain activation and muscle activation in healthy subjects while performing lower-limb exercise tasks. The results found a significant correlation between brain and muscle activation, highlighting the complex interaction between central and peripheral nervous mechanisms in motor control. The authors believe that these findings are important for clarifying motor control mechanisms and designing effective rehabilitation strategies. Clinically, this study holds significant promise for improving the management of KOA. By identifying specific brain regions that show altered activation patterns, we can potentially develop targeted interventions that address both the physical and neurological aspects of the disease. This could lead to more personalized treatment plans, enhancing patient outcomes and quality of life. A preliminary study by Hyochol et al. using fNIRS to measure the effects of transcranial direct current stimulation on patients with KOA has shown that central intervention is feasible and effective for KOA patients (Ahn et al., 2020). This study, by exploring the relationship between the clinical symptoms of patients with KOA and the relevant brain regions, may also contribute to the development of early predictive markers for KOA onset, facilitating timely interventions and better disease management.

However, this study also has its limitations. The cross-sectional design means that we cannot establish causality between brain activation patterns and KOA progression. Additionally, uncontrolled speed differences may confound neuromuscular and cortical activation patterns despite standardized pacing. Finally, the study is limited to a specific age range and severity of KOA, which may not be representative of all patient populations. Future studies should adopt longitudinal design to track dynamic neural adaptations relative to disease progression. Integrating speed as a covariate into a multivariate model to analyze its confounding effects. Large-sample stratified design that includes a broader age range and varying severities of KOA could provide more comprehensive insights into the disease’s impact on brain and muscle function.

In summary, this study aims to provide a detailed understanding of the brain activation patterns in KOA patients during different walking tasks. The innovative use of fNIRS and sEMG, combined with a robust methodology, ensures the feasibility and clinical relevance of this research. While the study has its limitations, the findings have the potential to significantly advance our understanding of KOA and inform the development of more effective intervention strategies.
